### Design

Individuals in the UIA follow-up cohort will be allocated to two groups, a modeling and a validation group, in a ratio of 2:1. Taking the annual rupture rate as 1% [2], the rate of loss would be less than 20%. The data will be analyzed statistically in the 5th years, the expectation being that at least 130 patients’ aneurysms will rupture in the first 4 years. The modeling group will be used to establish the risk of UIA rupture and compare relevant clinical information, radiological images, hemodynamic variables, genetic factors, HRMRI findings, and biomarkers [12, 13, 26–37] between the rupture and non-rupture groups to identify the risk factors for rupture. These will then be incorporated into a multi-dimensional model for predicting risk of UIA rupture. The validation group will then be used to validate that model (Fig. 2).

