This study will incorporate nested screening of 500 individuals from cohort 1 (CIAP-1). Recruitment for this study started in September 2016. The estimated primary completion date will be in December 2020. The project will produce preliminary results in the 5th year. After the end of the 5th year, we will have a longer follow-up visit to the patients who have been in the group.

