### Model building (first set of UIA queues)

The following possible or established risk factors for UIA will be collected and analyzed: age; sex; blood pressure, smoking, alcohol consumption, hyperlipidemia, diabetes mellitus, and family history of subarachnoid hemorrhage, intracranial aneurysm, and autosomal dominant diseases (polycystic kidney, Marfan syndrome, collagen dysplasia, etc.)The following imaging data will be collected and analyzed: shape, location, size, aspect ratio and odds ratio of aneurysms, morphological factors such as the angle of the aneurysm jet, and known risk factors for rupture.In our experience, follow-up angiography alone does not adequately predict the outcome whereas HRMRI is a more useful means of following these lesions [38]. We have also found and reported that aneurysm wall enhancement on HRMRI predicts instability of an intracranial aneurysm [39]. HRMRI will be performed on patients enrolled in the UIA follow-up cohort at the 20 participating centers and HRMRI-identified aneurysm wall enhancement assessed as a possible predictor of UIA rupture. Two-dimensional short-axis images of the aneurysms generated from the registered pre-and post-contrast T1w-SPACE images will be used to identify wall enhancement [13].To identify risk factors, the nested cohort study will incorporate the following: incidence of aneurysm rupture in the follow-up cohort, the definition of UIA recently rupture before the duration of follow-up was high risk of rupture of UIA, acquisition of imaging data for hemodynamic calculations; according to the aneurysm ratio of 1:2 UIA (rupture vs non-rupture), and analysis of differences in hemodynamic variables, genetic factors, and biomarkers.A.Analysis of hemodynamic variables: A three-dimensional shape will be created and image data from computed tomographic angiography, magnetic resonance angiography, or DSA saved as DICOM files. Once the 3D model has been reconstructed, it will be saved in an STL file format. A rigid wall in the parent vessel and aneurysm will be assumed in the simulation of hemodynamics. We will start by using ANSYS ICEM CFD (Materialise, Leuven, Belgium) to build a finite element model, then perform a simulation on ANSYS CFX software (Materialise), and finally use ANSYS CFX POST postprocessing to calculate Wall Shear Stress (WSS), maximum wall shear stress (WSSmax), low WSS areas, steady state of blood flow, and so on. Our team has already identified that these factors are associated with the stability of aneurysms [40–42].B.Gene and biomarker analysis: Blood samples will be collected from all participants and specimens of the aneurysm wall from patients who undergo craniotomy. Target chromosomes will be tested for blindly. Target genes and biomarkers identified as possibly relevant by the latest international research will be tested. Differences in genes and biomarkers between rupture and non-rupture groups will be compared to identify rupture-related factors.

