## Statistical methods

### Total sample size

CIAP-1: Calculation of the required sample size using an expected annual rupture rate of 1%, allowable error of d = 0.6%, and alpha = 0.05 on two-sided testing indicated that 1173 patients need to be enrolled per year, that is, 4692 over 4 years. An annual rupture rate of 1% [2] results in a loss rate of less than 20%. A reported hemodynamic index (complex flow patterns OR = 4.7) and HRMRI index (aneurysmal wall enhancement OR = 3.05 for ruptured versus unruptured aneurysm) also indicate that this sample size would be sufficient [12, 43]. Given that genetic factors have not yet been evaluated [35], our genetic testing will assess previously reported possible genetic indicators of prognosis; additionally, target genes and biomarkers will be selected according to the latest research progress in the future. In the 5th year of the study, we will analyze the data. As previously mentioned, at least 130 aneurysms are expected to rupture in the modeling group in the first 4 years. Allowing for a loss rate of 20%, the study will need to enroll 500 individuals.

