### Expected loss rate (less than 20%)

The expected loss includes all patient data excluded from the main analysis, usually because of a serious breach of the study protocol by the principal investigator (affecting the evaluation of the primary endpoint of effectiveness). Possible such breaches include failure to meet the inclusion/exclusion criteria; failure to follow the prescribed schedule; follow-up visits not occurring within the specified time limits, and concomitant treatments that may affect incidence of rupture. However, excellent clinical follow-up may achieve a drop-out rate of as little as 5%.

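### The 130 ruptures expected in the modelling group ignore the plan's own loss and staggered entry; the plan's inputs give about 50 to 67, and the 500 appears to be built on the 130

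*Protocol article*

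**What the plan says.** The Design section splits the follow-up cohort 2:1 into modelling and validation groups. It states "Taking the annual rupture rate as 1% [2], the rate of loss would be less than 20" per cent and continues with "the expectation being that at least 130 patients’ aneurysms will rupture in the first 4 years", naming no group. The Total sample size section refers back to that figure but places it in one group: "at least 130 aneurysms are expected to rupture in the modeling group in the first 4 years". The next sentence is "Allowing for a loss rate of 20%, the study will need to enroll 500 individuals".

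The same paragraph enrols 1173 patients per year, 4692 over 4 years, for CIAP-1; the Abstract gives that cohort as 5000. It also says that a hemodynamic index (odds ratio 4.7) and an HRMRI index (odds ratio 3.05) indicate a sufficient sample, with no power or exposure prevalence.

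On what the 500 are, the Abstract speaks of screening a cohort of 500 patients. Data collection and management says "This study will incorporate nested screening of 500 individuals from cohort 1 (CIAP-1"). Model building gives a 1:2 ratio of ruptured to non-ruptured aneurysms and refers to a nested study of the whole first cohort. On imaging it says "HRMRI will be performed on patients enrolled in the UIA follow-up cohort at the 20 participating centers".

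**The concern.** For a prediction model, the number of events is the quantity that governs how much can be estimated and validated. The plan states that number once without a group and once for two thirds of the cohort. Both cannot be the same 130 unless the whole-cohort figure is only a loose lower bound. The modelling-group figure also seems to leave out the 20% loss and the 4-year enrolment described in the same paragraph.

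If the count is too high, the nested 1:2 comparison, the model and its validation will all have fewer ruptures than the reader is told, and the 500 derived from the count has no footing.

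**Working it through.** **Inputs.** Rupture rate 1% per year (Design; Total sample size). Modelling share 2/3 (Design). Loss 20% (Total sample size); the best case is that "excellent clinical follow-up may achieve a drop-out rate of as little as 5" per cent (Expected loss rate). Cohort size 5000 (Abstract) or 4692 (Total sample size). Enrolment 1173 per year over 4 years (Total sample size). The Expected loss rate section defines loss as data excluded from the main analysis, so multiplying by 0.8 is a fair translation.

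**Formula.** Expected ruptures = N x 0.01 x mean years at risk x (1 - loss) x share. The compound form 1 - 0.99^t gives nearly the same (for example 79.6 instead of 80.0).

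**Step 1: reproduce the 130.** 5000 x 0.01 x 4 x 2/3 = 133. This needs all 5000 on day 1, 4 full years each, and no loss. With 4692 the same calculation gives 125. With 5% loss, 5000 gives 127.

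**Step 2: add loss and entry over 4 years.** By the end of year 4, mean follow-up is 2 years if entry is even, or 2.5 years if each year's patients all enter at its start.

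| N | Entry | Mean years | Whole, no loss | Whole, 20% loss | Modelling, no loss | Modelling, 20% loss |
|---|---|---|---|---|---|---|
| 5000 | day 1 | 4 | 200 | 160 | 133 | 107 |
| 4692 | day 1 | 4 | 188 | 150 | 125 | 100 |
| 5000 | start of year | 2.5 | 125 | 100 | 83 | 67 |
| 4692 | start of year | 2.5 | 117 | 94 | 78 | 63 |
| 5000 | even | 2 | 100 | 80 | 67 | 53 |
| 4692 | even | 2 | 94 | 75 | 63 | 50 |

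With staggered entry the modelling group yields 50 to 67 after loss (63 to 83 before). The validation third yields 75/3 = 25 to 100/3 = 33 after loss.

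**Step 3: later cut-off.** The analysis is planned in the 5th year. Running to the end of year 5 (mean 3 to 3.5 years) gives 75 to 93 in the modelling group after 20% loss, and 94 to 117 before. The only other route to 133 is 5000 x 0.01 x 5 x 0.8 x 2/3, that is, 5 full years for everyone, which is not the first 4 years.

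**Step 4: size needed.** For 130 in the modelling group with 20% loss: 130/(0.01 x 4 x 0.8 x 2/3) = 6094 patients if all have 4 years, and twice that, about 12,188, with even entry.

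**Step 5: where the 500 comes from.** 130 cases + 260 controls = 390, and 390/0.8 = 488, close to 500. The plan does not give this derivation, so it is an inference. At 1:2, a set of 500 calls for 500/3 = 167 ruptured cases before loss. The whole of CIAP-1 is expected to supply 94 to 125 by year 4 under staggered entry. Inflating for loss can add controls, but not ruptures that do not occur.

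**Step 6: the 500 as a followed cohort.** 500 x 0.01 x 4 = 20 with no loss and entry on day 1, and 16 after 20% loss. Staggered entry gives 500 x 0.01 x 2 = 10 to 500 x 0.01 x 2.5 = 12.5, or 8 to 10 after loss. The range is 8 to 20.

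**Step 7: sufficiency.** The plan gives no exposure prevalence, so 10% to 50% among controls is assumed. At 53 cases and 106 controls, two-sided 0.05, power for one binary factor is 70% to 91% for an odds ratio of 3.05 and about 95% or more for 4.7. At 5% exposure it is 49% and 80%. At 130 cases, power for 3.05 is about 97% or more over the 10% to 50% range.

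**The case against.** The strongest reply is that the Design section does not tie 130 to the modelling group. For the whole cohort of 5000, 4 full years each and 20% loss give 160, so 130 would hold as a lower bound. The plan also says that loss will be below 20% and may be as low as 5%. Part of this stands: the Design sentence alone is not wrong on that reading. But the Total sample size section places the figure in the modelling group, and enrolling 1173 per year over 4 years rules out 4 years of follow-up for everyone by year 4. Under staggered entry even the whole cohort falls short, with 94 to 125 before any loss.

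Two stronger conclusions are tempting, and the documents do not support either.

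- A reader might infer that the plan expects 130 ruptures from following 500 patients, which 1% per year rules out. The 1:2 ratio, the word nested and the reconstruction 488 all point to a sample drawn from CIAP-1, with cases from the larger cohort. Because the Abstract calls the 500 a cohort, the text is ambiguous, but this is not a demonstrated impossibility.
- A reader might infer that the claim of a sufficient sample is false. That sentence comes before the 130 and the 500 and rests on the two odds ratios. Step 7 shows that about 53 cases can still give reasonable power for a single factor. Without a stated power or exposure the claim is unsupported, and no more than that can be said.

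It might also be feared that too few patients will have HRMRI before rupture. Model building describes HRMRI in patients enrolled in the follow-up cohort, which suggests broad collection. The worry depends on how the role of the 500 is settled.

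**Conclusion.** The point holds for the event count. The stated 130 or more in the modelling group is about twice what the plan's inputs imply: 50 to 67 after 20% loss and 4-year enrolment. It stays out of reach with no loss (63 to 83), and with day-1 entry of all 5000 and 20% loss (107). These figures rest on a constant 1% rate, loss taken as a simple proportion, and roughly even enrolment.

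The group to which the 130 belongs differs between two sections. The 500, which appears to rest on the 130, has no valid event basis as written. The role of the 500 is unclear and the sufficiency statement is unsupported.

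**What to change.** - In Design and in Total sample size, replace the 130 with one expected count per analysis set, allowing for loss and staggered entry: about 75 to 100 ruptures in CIAP-1 by year 4, of which about 50 to 67 modelling and 25 to 33 validation. State the rate, loss and entry pattern used.
- Re-derive the 500 from that count and show the steps. At the plan's 1:2 ratio, 50 to 67 modelling cases take 100 to 134 controls, 150 to 201 analysable individuals in all. If the 500 is kept, its basis needs to be stated.
- Reconcile the Abstract, Design, Data collection and management, Model building and Total sample size on whether the 500 is a nested case-control sample with cases from all of CIAP-1, or a prospectively followed cohort. If it is a followed cohort, state that only about 8 to 20 ruptures are expected in it.
- Give the power and exposure prevalence behind the sufficiency statement, or withdraw it.

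The cost is a rewrite of a few sentences and a less favourable stated event count. No extra patients are needed.

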Risk factors for rupture, including hemodynamic variables, genes, and biomarkers will be calculated in a nested cohort study of the entire first cohort (CIAP-1: the first project of the China Intracranial Aneurysm Project and is managed by Tangdu Hospital, Fourth Military Medical University). A multi-dimensional model for predicting UIA rupture and bleeding that incorporates clinical, imaging, HRMRI data, and so on will be constructed by using a statistical model.Model validation: After establishment of the model, the second group of the follow-up cohort will be used for blind verification.Comparative analyses of histopathology of aneurysm walls: When participants undergo surgery for ruptured intracranial aneurysms, the sites of rupture will be identified intraoperatively and specimens of the aneurysm wall will be removed and preserved in formalin. The location of rupture, pathological damage, hemodynamic variables, HRMRI findings, and relevant biomarkers will be analyzed to identify differences between unruptured and unruptured aneurysms. Relationships between pathological damage, hemodynamic variables, and HRMRI features of the aneurysm wall will also be assessed.

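### As worded, the 500 CIAP-2 places are sized on the modeling group's ruptures alone and count no places for the validation group

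*Protocol article*

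**What the plan says.** - **Split.** The Design section has the follow-up cohort "allocated to two groups, a modeling and a validation group, in a ratio of 2:1". Risk factors are identified in the modeling group, including hemodynamic, genetic and biomarker variables, and the resulting model is validated in the other group.
- **Event count, first statement.** The Design section gives "the expectation being that at least 130 patients’ aneurysms will rupture in the first 4 years", with no group attached.
- **Event count, second statement.** Total sample size refers back to that figure but says "at least 130 aneurysms are expected to rupture in the modeling group in the first 4 years". The next sentence is "Allowing for a loss rate of 20%, the study will need to enroll 500 individuals".
- **Nested sampling.** Model building (first set of UIA queues) compares ruptured and unruptured aneurysms "according to the aneurysm ratio of 1:2 UIA (rupture vs non-rupture), and analysis of differences in hemodynamic variables, genetic factors, and biomarkers".
- **Scope of the nested study.** Later in the same section, the hemodynamic, gene and biomarker risk factors are to be calculated in a nested study of the whole first cohort, which the text identifies as CIAP-1.
- **Validation.** After that, "the second group of the follow-up cohort will be used for blind verification".
- **Who is measured.** The Abstract and the end of Data collection and management draw the 500 from CIAP-1 without naming a group. Data collection and management lists HRMRI, CFD and genetic findings with no limit by group. Model building takes blood from all participants and performs HRMRI in the follow-up cohort.

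**The concern.** Hemodynamic, genetic and biomarker predictors are what CIAP-2 adds to the parent registry. A model containing them can be scored in a validation patient only if that patient has those values. The number of places for this work is 500. If that number is built entirely from modeling-group ruptures and their controls, the plan promises validation of the full model without counting the patients it needs. In practice validation could shrink to the clinical, imaging and HRMRI part while the report describes the whole model as validated.

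There is a second problem. If the nested risk-factor study spans all of CIAP-1, validation patients help to choose the predictors. The validation is then no longer independent of model building, and its measured accuracy would tend to be optimistic.

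**Working it through.** **Inputs from the protocol article**
- Annual rupture rate 1%; loss below 20%, taken as 20% (Design; Total sample size).
- Parent cohort 5000 (Abstract; Aims); 4692 by the CIAP-1 calculation.
- Modeling to validation 2:1 (Design).
- Rupture to non-rupture 1:2 (Model building).
- 130 ruptures, 500 places (Total sample size).

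**Step 1. Reproduce the 500.** Cases plus two controls each: 130 × (1 + 2) = 390. With 20% loss: 390 / (1 − 0.20) = 487.5, rounded up to 488. This is 12 short of 500, or 2.4%. Multiplying instead, 390 × 1.2 = 468, fits less well. The article does not print this derivation. It is inferred from the match.

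**Step 2. Find which group the 130 belongs to.**
- Modeling share, four full years at risk, no loss: 5000 × 0.01 × 4 × 2/3 = 133 (131 with compounding).
- Whole cohort on the same basis: 5000 × 0.01 × 4 = 200, or 160 after 20% loss.

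The stated 130 matches the modeling share, as Total sample size says, and not the whole-cohort total.

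**Step 3. Places needed if 130 is the modeling count.**
- Modeling: 488 places, leaving 500 − 488 = 12.
- Validation ruptures at 2:1: 130 / 2 = 65.
- Validation nested set: 65 × 3 = 195; 195 / 0.8 = 243.75, rounded up to 244.
- Both groups: (390 + 195) / 0.8 = 731.25, rounded up to 732, which exceeds 500 by 232.

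**Step 4. Places if 130 covers both groups (the Design wording).**
- Total: 390 / 0.8 = 488, so both groups fit.
- Modeling: 130 × 2/3 = 87 ruptures; 260 / 0.8 = 325 places.
- Validation: 130 / 3 = 43 ruptures; 130 / 0.8 = 162.5, rounded up to 163 places.

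The 130 modeling ruptures in Total sample size are then not met.

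**Step 5. Split the 500 itself 2:1.**
- Places: 333 and 167.
- After 20% loss: 400 × 2/3 = 267 and 400 / 3 = 133.
- Ruptures at 1:2: 267 / 3 = 89 and 133 / 3 = 44.

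**Step 6. Check whether ruptures would fill these places.** This step assumes uniform entry of 4692 patients over four years, which the article does not state.
- To the end of year 4: 4692 × 2 = 9384 person-years; 94 ruptures; 75 after 20% loss; 75 × 3 = 225 patients.
- To the end of year 5: 4692 × 3 = 14,076 person-years; 141 ruptures; 113 after loss; about 338 patients (112.6 × 3).

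On these assumptions, nested sets from both groups together fit within 500.

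**The case against.** A reader might go further and infer that no validation patient will have hemodynamic, gene or biomarker values, so that the full model cannot be validated at all. The documents do not support that. No sentence says validation patients go unmeasured. The 500 are drawn from CIAP-1 as a whole, CFD and genetic findings are listed as data without limit by group, and blood is taken from everyone. Nor does the position of the nested comparison under Model building confine it to the modeling group, since the validation step sits under the same heading. This part of the objection stands. Collecting blood is not the same as assaying it, however, and none of these statements gives the validation group a share of the 500.

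The 130 × 3 / 0.8 route is also inferred, and the Design wording would let 488 cover both groups. That is fair, but it leaves the two sections in conflict and gives up the 130 modeling ruptures.

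Step 6 cuts both ways. With 75 to 113 ruptures in both groups together, modeling would not use up the 500. Equally, the 130 on which the 500 appears to rest would not be reached in either group. This makes the fix feasible but does not defend the stated figure.

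Finally, this is a condensed article, the figure showing the modeling and validation flow is not available here, and the full protocol may give the split. That would excuse silence about the split. It does not excuse a stated sample size, a stated basis and a stated validation that do not fit together.

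**Conclusion.** The point holds as a sizing gap and an internal contradiction. On the wording of Total sample size, the 500 counts about 488 modeling places and no validation places, where a 2:1 counterpart needs about 244 more (732 in all). On the wording of Design, both groups fit but modeling has about 87 ruptures instead of 130. Neither reading gives both 130 modeling ruptures and a measured validation set within 500.

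Separately, running the nested risk-factor study in the whole of CIAP-1 conflicts with blind validation in the second group. The phrase may have been meant to refer to the modeling set, but the text defines it as CIAP-1.

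The conclusion rests on the inferred derivation of the 500, on the 1:2 ratio applying in both groups, and on 20% loss. It does not extend to a claim that validation is impossible: the full model can be validated if validation patients are also assayed and counted.

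**What to change.** 1. Reconcile Design, Model building and Total sample size on which group the 130 describes and on where the nested study is run.
2. Fix each patient's modeling or validation label, at 2:1, before any nested sampling.
3. Draw the nested set (ruptures plus two non-rupture controls each) separately within each group, and use only the modeling set to select predictors.
4. Restate Total sample size with the expected ruptures and places per group within the 500. A 2:1 split of the 500 would give about 333 modeling and 167 validation places, or about 89 and 44 ruptures after 20% loss.
5. If validation patients will not have CFD, gene and biomarker values, limit the validation claim to the clinical, imaging and HRMRI part of the model.

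The cost is mainly wording. The 500 is unchanged, and blood is already collected from all participants. The real price is fewer nested places and a smaller stated rupture count for the modeling group (about 89 instead of 130), which leaves less information for choosing among many candidate predictors.
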